#### Eligibility Criteria

Samples for the quantitative research were recruited according to the following inclusion criteria: registered members of HPI Bali, age 55 years old or younger, working as a tour guide for 1 year or more, own a smartphone and/or computer with Zoom and WhatsApp applications, and familiar with Zoom and WhatsApp usage.

The exclusion criteria included the following: holding structural positions in HPI, having a formal health education background, unwilling to work as a tour guide after the reopening of tourism, and reluctant to participate in the study. In addition, the dropout criteria included those who did not fully participate in the intervention and could not be contacted due to illness or other reasons at the time of data collection.

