### Phase 2: Quantitative Study

#### Study Design

The research then continued with a quantitative strand using an experimental randomized pretest-posttest control group design. The intervention group received intervention in the form of a comprehensive travel health education model, while the control group received no intervention but standard health information provision.

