#### Participants

The minimum sample size in this study was calculated by employing the WHO Sample Size Determination software using the formula of a 1-tailed hypothesis test for a difference in two population means [37]. Using the parameters *d*=10.0, µ1=71.2, µ2=66.2, α=.05, and 1–β= 90% and taking into account a dropout rate of 10%, the minimum number of samples for each intervention and control group was 76. Sample selection was carried out with disproportionate stratified random sampling from the list of tour guides who were HPI Bali members. The selected tour guides were contacted to determine if they met the eligibility criteria. Those who did were given a further explanation of the research and asked to sign the informed consent form if they were willing to participate.

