#### Assignment of Intervention

A study statistician employed permuted block randomization technique to assign the participants to the intervention and control groups [38]. The research group assignment was communicated to the research team member, who informed and managed the participants’ enrollment and intervention assignment. A strategy to improve participants’ adherence to the intervention protocol was to elucidate the benefits of full participation in this study, including the provision of a completion certificate, credit for the internet, and compensation for the time allocated for participating in the online training. In addition, adherence monitoring was performed by inspecting the participants’ attendance and participation in each education session.

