#### Data Management and Analysis

Quantitative data were extracted from the digital questionnaires and transferred to the database. Coding was done to the extracted data, and data values were checked by two data analysts. Data without participants’ names were exported into a file format suitable for analysis with statistical software. The electronic data were stored on a computer protected with a password and only accessible to the research team.

Quantitative data will be analyzed descriptively by calculating the frequency distribution for categorical data as well as the total scores, mean, median, standard deviation, and range of minimum to maximum scores on numerical data. The comparability of the intervention group and the control group in terms of control variables will be analyzed using the chi-square test for categorical data and independent *t* test or Mann-Whitney *U* test for numerical data [39-41]. Data normality will be calculated using Kolmogorov-Smirnov test. Additionally, data homogeneity will be tested using the Levene test [39,42]. A complete case analysis will be performed to handle missing outcome data.

The mean comparison test will be conducted to determine mean differences between the intervention and the comparison groups. Repeated measures analysis of covariance (ANCOVA) will be employed because the measurement of dependent variables was conducted repeatedly at 5 time points, and there are covariates that need to be controlled in the analysis [39].

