WhatsApp information sharing was initiated in December 2021, a month after training. Participants were invited to a WhatsApp group and received weekly travel-related health information for 2 months. Participants asked questions and shared their experiences in the WhatsApp group. A moderator answered the questions and facilitated discussions among the participants. A total of 76 tour guides in the intervention group fully participated from the beginning to the end of the intervention (November 2021 to February 2022). An identical number of tour guides in the control group received no intervention but completed a series of self-administered questionnaires.

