Participation in the quantitative study was challenged by the fact that many tour guides have become jobless and are facing economic challenges due to COVID-19. Therefore, the participants were given internet credit and compensated for their time. All participants in the intervention and control groups fully participated in this study. No conclusions regarding the effectiveness of this model could be made because this study is still in the quantitative data analysis phase.

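### Incomplete participation in the intervention is listed as a dropout criterion; read as a separate criterion it can apply only to the intervention arm, and the article does not show that nobody was removed under it

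*Protocol article*

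**What the plan says.** All references are to the protocol article.

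- **Eligibility Criteria** (Phase 2) gives a rule that operates after enrolment: "the dropout criteria included those who did not fully participate in the intervention and could not be contacted due to illness or other reasons" when data were collected.
- **Study Design** (Phase 2) says that "the control group received no intervention but standard health information provision".
- **Assignment of Intervention** says that "adherence monitoring was performed by inspecting the participants’ attendance and participation in each education session".
- **Data Management and Analysis** gives the only rule for missing data: "A complete case analysis will be performed to handle missing outcome data". The article does not say whether all randomised guides are analysed in their assigned group whatever their attendance.
- **Participants** sets 76 per arm, a figure that already includes a 10% dropout allowance.
- **Results** reports that "A total of 76 tour guides in the intervention group fully participated from the beginning to the end of the intervention", and of the controls that "An identical number of tour guides in the control group received no intervention but completed a series of self-administered questionnaires".
- **Initial Findings** (Discussion) adds that "All participants in the intervention and control groups fully participated in this study".

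**The concern.** Attendance happens after randomisation, and education sessions exist in one arm only. A rule that turns incomplete attendance into dropout status therefore cannot act equally on the two arms. A control who is just as unmotivated has nothing to miss and stays in.

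Full participation meant ten hours of online training over two days and two months of weekly WhatsApp sharing. Five of the six outcomes are self-rated: attitude, subjective norms, perceived behavioural control, role identity and intention. The sixth, actual behavioural control, is a knowledge test. Willingness to complete the programme is plausibly related to several of these. If less engaged guides were left out of the intervention arm alone, its mean could rise for reasons unrelated to the education, and randomisation would no longer protect the comparison. The article itself concedes, under Strengths and Limitations, that self-reported answers may be normative.

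**Working it through.** **1. The plan's own figure.** Inputs from Participants: means 71.2 and 66.2 (difference 5.0), one-sided α 0.05, power 90%, and 10.0 printed as *d*, read here as the standard deviation.

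n = 2 × [10 × (1.645 + 1.282) / 5]² = 68.5, so 69 per arm.

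Allowance for dropout: 69 × 1.10 = 75.9, so 76 (69 / 0.90 = 76.7, so 77). The stated 76 is reproduced, which supports reading *d* as the SD. The target before dropout was 69, so 76 is the inflated figure.

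**2. Which arm each limb can reach.**

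| Limb of the dropout criteria | Intervention | Control |
|---|---|---|
| Did not fully participate in the intervention | can apply | cannot apply: no sessions |
| Could not be contacted at data collection | can apply | can apply |

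Only the first limb is one-sided.

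**3. What the reported counts can show.** 76 full participants per arm fits two histories:
- exactly 76 per arm were randomised and nobody was lost, in which case the bias is zero;
- more were randomised and some were classed as dropouts or replaced until 76 was reached.

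No separate number randomised per arm is given, so the counts do not distinguish the two.

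**4. Size if guides were removed.** Neither the share removed nor the correlation is in the documents. Assume that the least adherent 10% of the intervention arm is removed, that adherence correlates *r* with the outcome, that the SD is 10, and that there is no true effect. For a truncated normal distribution:

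bias = r × φ(−1.2816) / 0.90 × SD = r × 0.1755 / 0.90 × 10 = 1.95 r points.

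With 68 against 76 guides, SE = 10 × √(1/68 + 1/76) = 1.67. The one-sided false-positive rate is 1 − Φ(1.645 − bias/SE).

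| r | Bias (points) | Share of planned 5 points | One-sided error (nominal 5%) | Two-sided error (nominal 5%) |
|---|---|---|---|---|
| 0.2 | 0.39 | 8% | 7.9% | 5.6% |
| 0.3 | 0.58 | 12% | 9.8% | 6.4% |
| 0.5 | 0.97 | 20% | 14.4% | 9.0% |

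The one-sided column matches the sample-size calculation, made "using the formula of a 1-tailed hypothesis test for a difference in two population means".

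A second parameterisation does not use *r*. If a share f is removed and those removed score g points below the rest, the bias is f × g:
- f = 5%, g = 2.5 to 10: 0.13 to 0.5 points
- f = 10%, g = 2.5 to 10: 0.25 to 1.0 points
- f = 20%, g = 2.5 to 10: 0.5 to 2.0 points
- f = 0: zero

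**5. Effect of using the baseline.** The table treats the outcome as an unadjusted post-test mean. The article plans a before-after comparison and a repeated measures ANCOVA over five time points. If adherence correlates equally with the baseline and later scores, selection raises both alike and the bias in change is zero. If baseline is a covariate and the pre-post correlation is assumed to be 0.5, the r = 0.3 bias falls from 0.58 to 0.58 × (1 − 0.5) = 0.29 points. What remains is selection related to change itself, which the documents give no means of estimating.

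**6. Power.** Loss of numbers is not the issue: 68 against 76 guides still gives 91.2% one-sided power, against 92.5% with 76 per arm.

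**The case against.** There are four serious objections.

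- **The sentence joins its two limbs with the word and.** Read literally, a guide is a dropout only if both apply, which is ordinary loss to follow-up. This reading is possible. But the exclusion criteria just before it are also joined by and, although each is plainly sufficient alone, so separate criteria are at least as natural a reading. The wording needs settling either way.
- **Removal from the analysis is inferred.** The complete-case rule covers missing outcomes only. A guide who missed a session but returned all five questionnaires has none missing and would not be omitted by that rule. This stands: a reader might infer that complete-case analysis discards non-attenders, and the text does not say so. What supports the inference is weaker: dropout status appears among the eligibility rules, and the sample was inflated for dropout.
- **The article reports full participation in both arms.** A reader might conclude that the randomised comparison has been broken. The documents do not support that; taken at face value they point to no removals. What remains is that a statement about all participants would also be true if others had already been classed as dropouts.
- **Analysis sets and participant flow are commonly left to fuller documents.** That is fair, and their absence is not the point here. The point is the rule that the article does state.

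**Conclusion.** The concern holds as a conditional one. Read as a separate criterion, incomplete participation is an asymmetric post-randomisation rule. If it were used to leave guides out of the analysis, it could bias the comparison towards the intervention.

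The realised bias may well be zero, given the full participation reported. The article cannot confirm this, because the completers equal the dropout-inflated target and the number randomised is not stated separately.

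If 10% had been removed, with r between 0.2 and 0.5, the bias would be about 0.4 to 1.0 points (8% to 20% of the planned difference) on unadjusted post-test means, and smaller once baseline is used. Both inputs are assumptions. Severity is moderate: the wording should be corrected and the counts confirmed, but nothing shown establishes that the result is distorted.

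**What to change.** 1. Take incomplete participation out of the dropout criteria, so that dropout means only missing outcome data.
2. State that the main analysis includes all randomised guides in their assigned group, using every questionnaire they returned, whatever their attendance.
3. Report attendance as adherence, and keep a completers-only analysis as a sensitivity analysis.
4. State the number randomised per arm and confirm that none was removed or replaced. If any were, bring their returned questionnaires back into the main analysis.

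The cost is a change of wording and the use of data already collected; the article describes the quantitative analysis as still under way. If nobody was removed, the result does not change. If some were, the estimate may be slightly smaller.

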#### Assignment of Intervention

A study statistician employed permuted block randomization technique to assign the participants to the intervention and control groups [38]. The research group assignment was communicated to the research team member, who informed and managed the participants’ enrollment and intervention assignment. A strategy to improve participants’ adherence to the intervention protocol was to elucidate the benefits of full participation in this study, including the provision of a completion certificate, credit for the internet, and compensation for the time allocated for participating in the online training. In addition, adherence monitoring was performed by inspecting the participants’ attendance and participation in each education session.

#### Study Outcomes

The outcomes of this study referred to the constructs of integrated TPB and identity theory, including attitude, subjective norms, perceived behavioral control, actual behavioral control, behavioral intention, and role identity. A summary of the outcomes is presented in Table 1.

In addition to those outcome variables, several variables were controlled by analysis, namely age, sex, education, length of work, employment status, tourists’ country of origin, and type of tourism activities.

**Table 1 table1:** Summary of study outcomes.

Study outcomes	Definition	Data measurement and analysis scale	Data source (time point)
Attitude	Psychological tendencies expressed by the tour guides regarding providing travel health information to tourists	Measurement scale: ordinal (Likert scale) Data analysis scale: interval	Self-administered questionnaire (T_0_, T_1_, T_2,_ T_3,_ T_4_)
Subjective norms	Tour guides’ perception of the extent to which providing travel health information to tourists is something that is expected by the tourists they serve, their employers (travel agents), HPI^a^, and the community	Measurement scale: ordinal (Likert scale) Data analysis scale: interval	Self-administered questionnaire (T_0_, T_1_, T_2,_ T_3,_ T_4_)
Perceived behavioral control	Tour guides' confidence in their ability to provide travel health information to tourists	Measurement scale: ordinal (Likert scale) Data analysis scale: interval	Self-administered questionnaire (T_0_, T_1_, T_2,_ T_3,_ T_4_)
Actual behavioral control	Tour guides’ knowledge regarding the prevention and first aid of travel health problems	Measurement scale: ordinal (Likert scale) Data analysis scale: interval	Self-administered questionnaire (T_0_, T_1_, T_2,_ T_3,_ T_4_)
Role identity	Tour guides’ perception of the extent to which travel health promotion is a part of their role	Measurement scale: ordinal (Likert scale) Data analysis scale: interval	Self-administered questionnaire (T_0_, T_1_, T_2,_ T_3,_ T_4_)
Behavioral intention	Tour guides’ willingness to provide travel health information to the tourists they serve	Measurement scale: ordinal (Likert scale) Data analysis scale: interval	Self-administered questionnaire (T_0_, T_1_, T_2,_ T_3,_ T_4_)

^a^HPI: Himpunan Pramuwisata Indonesia (Indonesian Tour Guide Association).

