**Methods:**

This is an exploratory sequential mixed methods research. The first phase consisted of a qualitative study with an informed grounded theory design. In-depth interviews were carried out with tour guides from all language divisions and policymakers of the Indonesian Tour Guide Association Bali Branch or Himpunan Pramuwisata Indonesia Daerah Bali (HPI Bali). The interview guidelines were developed based on the theory of planned behavior and identity theory. Qualitative data were analyzed thematically. In the interim phase, a travel health education model and questionnaire were developed based on the qualitative findings. The initial model and its instruments were finetuned after consultation with travel medicine and health promotion experts. Furthermore, the validity and reliability of the questionnaire were tested on 30 tour guides. The second phase consisted of a quantitative study with a randomized pretest-posttest control group design. A total of 76 tour guides in the intervention group received comprehensive travel health education, while 76 in the control group received no specific intervention. Outcome variables (ie, attitudes, subjective norms, perceived behavioral control, actual behavioral control, role identity, and behavioral intention) were measured at baseline (T_0_), after the online training (T_1_), before information sharing via WhatsApp (T_2_), a month after the start of the WhatsApp intervention (T_3_), and at the end of the WhatsApp intervention (T_4_). The mean difference of each outcome variable before and after the intervention will be compared between the intervention and control groups. Thereafter, the quantitative and qualitative findings will be integrated into a joint display.

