### Conclusions

This exploratory sequential mixed methods study aims to develop a comprehensive, relevant, and effective travel health education model for tour guides to improve their travel health promotion behavior. A travel health education model comprising online training and information sharing via WhatsApp was developed based on the qualitative findings and in consultation with experts. The intervention was trialed with tour guides, and a series of self-administrated questionnaires was completed. After the completion of quantitative data analysis, the qualitative and quantitative findings will be integrated into a joint display to conclude on the efficacy of the education model.

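### Six outcomes of equal rank feed one efficacy conclusion, with no primary outcome, time point or contrast named and a sample size tied to none of them

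*Protocol article*

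**What the plan says.** Study Outcomes (Phase 2) gives the outcomes as the constructs of the integrated theory, "including attitude, subjective norms, perceived behavioral control, actual behavioral control, behavioral intention, and role identity". Table 1 shows all six with the same schedule, T0 to T4, and ranks none above another. The end of the Introduction's Background likewise gives all six as efficacy targets.

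The Abstract says that "The mean difference of each outcome variable before and after the intervention will be compared between the intervention and control groups". Data Management and Analysis names repeated measures ANCOVA over the five time points, without saying which contrast from that model answers the question.

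The sample size (Participants) comes from a "1-tailed hypothesis test for a difference in two population means" with "µ1=71.2, µ2=66.2, α=.05, and 1–β= 90" per cent and *d*=10.0. It concludes that, "taking into account a dropout rate of 10%, the minimum number of samples for each intervention and control group was 76". No outcome or time point is attached to the two means.

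The closing Conclusions section says that "the qualitative and quantitative findings will be integrated into a joint display to conclude on the efficacy of the education model". Future Directions says much the same. Neither says how many outcomes must favour the intervention, or at what time.

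**The concern.** The stated alpha of .05 and power of 90% are both true only of one specified comparison. Here six comparisons have equal standing and one overall conclusion is drawn from them, so the two properties attach to nothing in particular.

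A single mean and SD pair is also unlikely to describe all six scores. According to Questionnaires, five outcomes use 7-point agreement items, while actual behavioral control uses knowledge items answered right, wrong or do not know. Unless all are rescaled, which the article does not say, 71.2, 66.2 and 10 must belong to one particular score that the reader cannot identify.

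At stake is the trial's main message. Without a named primary or a decision rule, whichever outcome or time point looks best can be presented as evidence of efficacy.

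**Working it through.** **Inputs from the article.** Means 71.2 and 66.2, so a difference of 5.0; SD 10.0 (written *d*, read as the SD because that reproduces the sample size); one-sided alpha .05; power 90%; dropout 10%; 76 per group (all Participants). Six outcomes (Study Outcomes). Four post-baseline times (Data Collection, Phase 2).

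**Inputs that are assumptions.** The correlation between the six test statistics is not given, so a range from 0 to 0.9 is shown. The article states no test level for the analysis; .05 is carried over from the sample-size sentence. The rule that any one positive result means efficacy is also an assumption.

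**1. Reproduce the plan's figure.**
n per group = 2 × [SD × (z0.95 + z0.90) / difference]² = 2 × [10 × (1.645 + 1.282) / 5]² = 68.5, so 69.
With dropout: 69 × 1.1 = 75.9, so 76; or 68.5 / 0.9 = 76.1. The stated 76 is reproduced. The two-sided version gives 85 (94 to 95 with dropout) and does not match. The number is therefore sound for exactly one one-sided comparison.

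**2. Chance of at least one false positive among six tests.** There is one test per outcome at .05 and no true effect on any outcome.
Independent: 1 − 0.95⁶ = 26.5%.
Equally correlated with correlation ρ: 1 − ∫ φ(u) [Φ((1.645 − √ρ·u) / √(1 − ρ))]⁶ du for the one-sided test, with the matching two-sided form.

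| Correlation | One-sided | Two-sided |
|---|---|---|
| 0 | 26.5% | 26.5% |
| 0.3 | 22.0% | 24.1% |
| 0.5 | 18.6% | 20.7% |
| 0.7 | 14.8% | 16.4% |
| 0.9 | 10.0% | 10.8% |

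**3. If each post-baseline time were also tested.** Simulating 6 × 4 tests at .05, with assumed between-outcome correlation 0 to 0.7 and between-time correlation 0.5 to 0.7, gives about 31% to 61% one-sided and 38% to 64% two-sided. The article does not say that it will do this.

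**4. The opposite rule.** If all six had to be positive, the false-claim rate would be controlled, but power could fall to 0.9⁶ = 53% if the outcomes were independent with 90% power each. It would be higher if they were correlated.

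**5. Price of controlling the error.** At the strictest Holm step, one-sided .05/6 = .00833 (z = 2.394), with 76 per group:
unadjusted: 5 / (10 × √(2/76)) = 3.082; 3.082 − 2.394 = 0.688; power about 75%, against 92% at .05.
adjusted for T0 with an assumed correlation of 0.5: residual variance 100 × (1 − 0.25) = 75, SD 8.66; 5 / (8.66 × √(2/76)) = 3.559; 3.559 − 2.394 = 1.165; power 88% by the normal approximation and 87% by the noncentral t.
Holding 90% unadjusted power at .05/6 would have needed 109 per group, or 120 to 122 with dropout.

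**The case against.** This is a condensed article, and a multiplicity rule may stand in an analysis plan that is not shown. The absence of such a rule is not the point here. The primary outcome and the outcome behind the sample size are protocol content, and the article gives a full outcomes table and a full sample-size statement without connecting them.

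A reader might infer that the plan tests each outcome at .05 at several times and claims efficacy from any single success, so that a 16% to 26% false-claim rate is a property of the plan. The text does not support that. The .05 appears only in the sample-size sentence. No any-success rule is written, and the overall conclusion is to be reached through a joint display of quantitative and qualitative findings. The 16% to 26% figure counts one two-sided test per outcome, whereas the article's own test is one-tailed. A repeated measures ANCOVA can yield one group or group-by-time test per outcome. The 71% obtained from 24 independent tests (1 − 0.95²⁴) needs per-time testing that is not planned, and independence among repeated measures on the same people.

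One could also argue that each construct is a separate question and needs no joint control. That would be reasonable if six separate conclusions were drawn, but the article announces one.

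Finally, behavioral intention is not the only possible primary. In Theoretical Foundation, attitude, subjective norms and perceived behavioral control act through intention, but actual behavioral control stands beside it as a determinant of behavior. Nothing shows that 71.2, 66.2 and 10 are intention scores either.

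**Conclusion.** The concern holds in conditional form. What the document itself shows is that six outcomes have equal rank, no primary outcome, time point or contrast is named, and a correctly computed sample size belongs to none of them.

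The size of the problem depends on how the results are read. With one one-sided test per outcome at .05, no true effects, and any positive result taken as efficacy, the false-claim probability is about 15% to 26% for correlations from 0.7 down to 0. Even at 0.9 it is about 10%, twice the nominal level. It would be higher with separate tests at each time. The correlations are assumed, since the article gives none.

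**What to change.** 1. State which outcome, scale and time point the figures 71.2, 66.2 and 10 describe. Only the authors can supply this; the figures should not be assigned to an outcome afterwards.
2. The article places the study in quantitative analysis in April 2022, so the default should not depend on choosing a favoured outcome now. Base the efficacy conclusion on one between-group contrast per outcome at T4, adjusted for T0, with Holm over all six at an overall .05. Report T1 to T3 as supportive.
3. Only if group results are still unseen, name one primary outcome at T4 and test it at .05. Behavioral intention is one defensible choice, since three of the other constructs act through it in the article's theory and behavior itself could not be measured. Test the other five with Holm only if the primary is significant. Without that gate, alpha is spent twice: up to 1 − 0.95² = 9.75% under independence.
4. Say in the Conclusions that the efficacy statement follows from this procedure.

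The cost is analysis wording and a stricter threshold, with no new data. At the strictest Holm step, power for a 5-point difference with 76 per group is about 75% unadjusted, or about 87% with T0 adjustment if that correlation is 0.5. With a single primary, the existing 76 per group still suffices for that outcome, provided that the sample-size figures apply to it.
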